### Sample Size

The number of participants to be included is not based on an a priori calculation. This is due to the absence of data in the literature regarding the effectiveness of a primary prevention program in the military context, measured using a composite criterion that encompasses affect, self-compassion, and hardiness. In order to determine the sample size needed to observe a significant between-group difference, we used the following parameters: a 2-tailed statistical test; a 55% response rate in the intervention group; a 30% response rate in the nonintervention group (significance *P*=.50; power =0.80). If we take into account potential dropouts (estimated at 20%), each group should consist of 58 individuals, making a total of 116 participants.

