### Statistical Methods

Continuous variables will be presented as mean and SD, if the distribution is normal (the Shapiro-Wilk test will be used, if necessary). In case of a nonnormal distribution, data will be presented as median, quartiles, and extreme values. Scale variables will be treated as ordinal data and analyzed as above. Depending on the analysis, data may be classed as categorical variables. Categorical variables will be expressed as absolute values and percentages. To control for attrition, calculations will assume 20% of data are missing.

The primary analysis will examine the effectiveness of the prevention program. This will be evaluated by comparing the percentage of responses between intervention and nonintervention groups, using a *χ*^2^ test. Secondary analyses will examine the abovementioned markers. Values for the intervention and the nonintervention group will be compared using a repeated measures ANOVA if the conditions for applying an ANOVA are met. Vulnerability will be initially identified using a cluster analysis of the measured biological variables (a *k*-means or Gaussian model mixture, depending on the distribution). The analysis will seek to identify the most biologically at-risk cluster (vulnerable compared with nonvulnerable). The effect of the intervention as a function of vulnerability status will be evaluated using repeated measures ANOVA, by comparing vulnerable and nonvulnerable groups. Psychosocial variables will be compared between intervention and nonintervention groups using repeated measures ANOVA, if the conditions for its application are met. A regression analysis will aim to test the mediating role of psychosocial determinants in the improvement of the composite score.

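### The sample-size figures do not reconcile: alpha is printed as .50, and 58 per group cannot both include 20% dropout and give 80% power at two-sided .05

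*Protocol article*

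**What the plan says.** The Sample Size section of the protocol article sets out these elements:

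- The test and the rates: "a 2-tailed statistical test", "a 55% response rate in the intervention group" and "a 30% response rate in the nonintervention group".
- The error rates: "significance *P*=.50; power =0.80".
- The result: "If we take into account potential dropouts (estimated at 20%), each group should consist of 58 individuals, making a total of 116 participants". The 58 is thus presented as the number after the dropout allowance.

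The same section opens by saying that the number does not come from an a priori calculation, for want of published data on such a programme, and then gives one.

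Statistical Methods names a chi-square test on the percentage of responders as the primary analysis and repeats the attrition assumption: "To control for attrition, calculations will assume 20% of data are missing". Under Primary End Point, the composite is evaluated at 4 months. No other alpha, no formula and no number before dropout appear in the article.

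**The concern.** Two things look wrong. A significance level of .50 is not usable for a primary test, and 58 does not follow from it. If the conventional two-sided .05 is put in its place, 58 is what a standard formula returns with no dropout allowance at all, yet the text says the allowance is included.

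This is the only power statement for the primary endpoint. If the achievable power is well below 80%, a real 25-point benefit would be missed more often than the plan implies, and a null result would be read as if it came from an 80%-power trial. A reader also cannot reproduce the design from the printed parameters.

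**Working it through.** **Inputs.** From Sample Size: p1 = 0.55, p2 = 0.30, two-tailed, power 0.80, dropout 20%, 58 per group. From Statistical Methods: chi-square test. Assumed: alpha = .05, since .50 is unusable and no other value is given.

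Constants: p1(1−p1) + p2(1−p2) = 0.2475 + 0.21 = 0.4575. The difference is 0.25 and its square is 0.0625. The mean rate is 0.425, so 2 × 0.425 × 0.575 = 0.48875. z for 80% power is 0.8416.

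**1. Does the printed alpha give 58?** With two-sided .50, z = 0.6745.

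- Unpooled: (0.6745 + 0.8416)² × 0.4575 / 0.0625 = 16.8, so 17.
- Pooled: 17.3, so 18.
- After 20% loss: 22 or 23. The printed alpha does not give 58.

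**2. Number needed at two-sided .05 (z = 1.96), before dropout.**

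- Unpooled: (1.96 + 0.8416)² × 0.4575 / 0.0625 = 57.45, so **58**. This equals the printed number.
- Pooled, matching the chi-square test: (1.96 × √0.48875 + 0.8416 × √0.4575)² / 0.0625 = 60.2, so **61**.

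**3. Number needed after 20% loss.**

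- 58/0.8 = 72.5, so 73 per group (146 in total).
- 61/0.8 = 76.25, so 77 per group (154 in total).
- Against these, 116 is 30 to 38 short.

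**4. Other routes to 58.** At two-sided .10 (equivalently one-sided .05), the unpooled formula gives 45.3, so 46, and 46/0.8 = 57.5, so 58. The pooled formula gives 48, and 48 × 1.2 = 57.6, so 58. On either route the dropout has been added (in the second by multiplying rather than dividing), and the mismatch lies in the alpha or the sidedness.

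**5. Power if 116 enrol and 20% are lost.** 58 × 0.8 = 46.4, so 46 evaluable per group. At two-sided .05:

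| Method | 58 evaluable | 46 evaluable |
|---|---|---|
| Unpooled formula | 80.4% | 70.8% |
| Pooled formula | 78.5% | 68.5% |
| Exact enumeration, chi-square | 78.4% | 67.6% |

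With a continuity correction or Fisher's test, power at 46 per group is about 60%. By exact enumeration of the chi-square test, 46 per group reach 80% only at about 59% against 30%.

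**6. Independence.** All these figures treat soldiers as independent. The Randomization section says individual randomization is not feasible, and Participant Timeline describes briefing two companies. As an illustration only, assume an intraclass correlation of .01 and one company of 46 per arm. The design effect is 1 + 45 × 0.01 = 1.45, the effective number is 46/1.45 = 31.7 per group, and pooled power is about 52%.

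**The case against.** The strongest objection concerns cause. A reader might infer that the 20% was simply never added. The article does not establish that: it gives no number before dropout and no usable alpha, and the two-sided .10 route reaches 58 with the allowance included. This objection stands as to the origin of the error. It does not rescue the stated power, because that route departs from a two-tailed test at .05, and on either route power at two-sided .05 after 20% loss is about 68% to 71%.

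A reader might also take 68% as the power of this trial. That is not supported either, since it assumes independence in a design without individual randomization. It can only serve as an upper bound.

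The section does not say when the 20% is lost. If part of it falls after month 4, more than 46 per group would be evaluable for the primary endpoint. At 10% loss, 58 × 0.9 = 52.2, so 52 per group, and pooled power is 74%, still below 80%.

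It would be too strong to say that the printed .50 invalidates the primary test. It is an evident misprint, and Statistical Methods, which defines the test, sets no such threshold.

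Finally, the sentence denying an a priori calculation can be read as admitting that the assumed rates have no empirical basis. That reading is fair, but it does not correct the arithmetic.

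**Conclusion.** The point holds. The printed alpha of .50 is wrong as written, and 58 per group cannot both absorb 20% dropout and deliver 80% power for 55% against 30% in a two-tailed test at .05. The number is most likely the uninflated one, but this cannot be proved from the article.

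With 116 enrolled and 20% lost before month 4, power is at most about 68% for the planned chi-square test (70.8% by the unpooled formula). The type II error is therefore about 32% rather than 20%, so a true 25-point difference would be missed in roughly one trial in three. This rests on alpha .05, the full 20% loss falling before the 4-month evaluation, and independent individuals. Any positive correlation within companies lowers the power further.

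**What to change.** In Sample Size:

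1. Correct the significance level to the value intended (two-sided .05), and state the formula used and the number per group before dropout.
2. Keep 116 as the enrolled number. Restate power as at most about 68% to 71% for 55% against 30% after 20% loss (46 per group), with 80% reached only at about 59% against 30%. Say that these figures assume independent individuals.
3. Reword, rather than delete, the sentence on the absence of an a priori calculation, so that it says the assumed response rates have no empirical source.

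For information, keeping 80% under the chi-square test would need about 77 per group (154 in total), again assuming independence. Enrolling 73 per group would leave 58 evaluable and about 78.5% power by the pooled formula.

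The cost is wording and a less favourable stated power. Restating the power needs no extra participants.

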## Results

The project is currently ongoing, and results are expected to be published by the end of 2024.

## Discussion

This project aims to evaluate an interventional research program for the primary prevention of occupational health problems. The program is as comprehensive as possible and synergistically links physiological, psychological, and social factors. We hope that the integration of biopsychosocial factors, which are suited to the characteristics of the occupational environment, will reinforce the effectiveness of current strategies. The project respects the three pillars of evidence-based prevention: (1) it investigates what is the best evidence and contributes to research-based knowledge; (2) it considers experiential knowledge; and (3) it takes into account the values, preferences, and characteristics of populations and individuals. This type of primary prevention intervention could provide a framework for other interventions that can be modified and adapted to different professional contexts. Data regarding transfer and feasibility collected during our study with operational military personnel could be used in further work to optimize the program for other army corps. Finally, it is imperative to stress that this study adopts an ecological approach, that is, it strives to reflect as closely as possible the real-life experiences of French army soldiers. This approach is essential to obtain information directly applicable to their daily routines and challenges. However, it is essential to recognize that there are potential limitations inherent in this approach, particularly with regard to adherence to the research protocol. Operational constraints within the military environment can sometimes override the ideal execution of the research program. These constraints may require adjustments to the protocol to ensure practicality and feasibility. For example, modifications in the number and frequency of workshops may be necessary to meet service needs and requirements, without compromising operationality. However, the encouraging exploratory results and the interest shown by the military personnel observed by [name] [24] mean that we can be confident that this study will provide a better understanding of the field of PTSD prevention in the military.

The research team is committed to maintaining the integrity of the study while adapting flexibly to these challenges, in order to obtain meaningful and relevant results that will contribute to the well-being and effectiveness of our soldiers in the French army.

## Appendix

Multimedia Appendix 1 Workshop schedule.

Multimedia Appendix 2 Questionnaires used for the primary composite end point.

Multimedia Appendix 3 Genetic polymorphisms involved in stress regulation mechanisms studied in the project.

Multimedia Appendix 4 miRNAs targeting regulatory phenomena established by earlier work and studied in the project.

## Abbreviations

BMS: Burnout Measure Short Version
DRS-15: Dispositional Resilience Scale
HADS: Hospital Anxiety and Depression Scale
ICPH: inner correspondence and peaceful harmony
MSPSS: Multidimensional Scale of Perceived Social Support
OPEX: external operation
PANAS: Positive and Negative Affect Scale
PCL-5: Posttraumatic Checklist-5
PHQ-15: Patient Health Questionnaire
PREPAR: Primary Prevention of Posttraumatic Stress Disorder in Military Professionals
PSS: Perceived Stress Scale
PTSD: posttraumatic stress disorder
TE: traumatic event
